### 3.1.7 Outcome Measures

In this phase of the study, outcome measures will be evaluated at two distinct intervals:

1. Baseline (pre-intervention): These assessments are conducted before the intervention to establish the initial state of participants' KOA condition.
2. Immediately post-completion of the intervention (short term, week-8): These measurements are taken immediately after the last intervention, occurring at week 8.
3. Follow-up (long-term, week-12): The assessments are conducted after the intervention occurring three months after the final treatment session at week 24.

All outcomes will be assessed by a blinded assessor not involved in carrying out the intervention. Additionally, participants will be screened for potential adverse events, such as bruising, fatigue, weakness, and swelling, during each follow-up visit throughout the treatment. The outcomes to be measured in the study include:

1. Knee Injury and Osteoarthritis Outcome Score (KOOS): This validated questionnaire assesses the outcomes and subjective experiences of individuals with knee injuries or osteoarthritis, encompassing domains like pain, symptoms, activities of daily living, sports and recreation, and quality of life. The KOOS demonstrates high reliability and validity in different languages, with excellent test-retest reliability (intraclass correlation coefficients ranging from 0.91 to 0.99)(Phatama et al., 2021). Please refer to the Appendix 1.
2. Active knee flexion Range of Motion (ROM): Knee flexion will be measured using a goniometer, with high reliability (intraclass correlation coefficient (ICC) of 0.997 for knee flexion)(Remigio et al., 2017). The goniometer is reliable for evaluating knee flexion in various positions, including supine, prone, and sitting positions, with highly correlated results ( $r > 0.80$ ) (Unver et al., 2009).
3. Timed Up and Go (TUG) test: This test assesses functional mobility by measuring the time required to stand from a chair, walk 3 meters, and sit again. The TUG test is chosen for its high reliability and validity in Grade 1-3 KOA, with a minimal detectable change of 1.10 seconds (Chen et al., 2022). OARSI recommends the TUG test for KOA patients, with strong intra-rater and inter-rater reliability values (0.97 and 0.96, respectively) (Alghadir et al., 2015).
4. Numeric Pain Rating Scale (NPRS): This is a tool commonly used to assess pain intensity, utilizing an 11-point scale ranging from 0-10. In this scale, 0 signifies “no pain” while 10

represent the “worst imaginable pain”. The individual are asked to select a single number from this scale that most accurately reflects their current level of pain. A study reported excellent reliability for NPRS with ICC of 0.95.(Alghadir et al., 2018)

5. Knee radiographic imaging, involving X-ray examinations, will be employed to quantitatively assess changes in knee joint structure damage. The examination will only be conducted during baseline and follow-up interval. A qualified radiologist will conduct the knee X-ray examinations to ensure standardized assessments and minimize assessor bias (Lopes et al., 2023) . The evaluation will focus on key parameters, including joint space width, which measures the distance between the femur and tibia to assess joint space narrowing; joint alignment, involving the assessment of angles like the mechanical axis of the leg to identify varus or valgus deformities; and cartilage thickness, measuring articular cartilage thickness in specific knee joint regions to monitor cartilage loss.

The utilization of X-rays as an outcome measure aims to evaluate the severity and progression of KOA by examining changes in joint space, the presence of osteophytes, and the degree of bone or joint destruction(Yang et al., 2022). X-rays are a widely used diagnostic tool for KOA in clinical practice, offering an objective measure of disease progression over time (El-Ghany et al., 2023). The choice of X-rays is practical due to their relatively low cost and widespread availability in clinical and research settings. Extensive research has demonstrated the reliability and validity of using X-rays to assess KOA, showing high inter-observer reliability and moderate-to-high validity compared to other imaging modalities such as MRI or ultrasound (Paraskevas et al., 2023).

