## 1.0 Introduction

### 1.1 Study background

Knee osteoarthritis (OA) is a common cause of knee pain worldwide, which is caused by repetitive stress and mechanical trauma leading to an inflammatory process within the knee joint, resulting in articular cartilage deterioration and loss of chondrocytes (Geng, Li et al. 2023). The primary method of dealing with musculoskeletal pain involves conservative techniques that include both pharmaceutical and nonpharmacological therapies. Recent research has demonstrated the effectiveness of nonpharmacological interventions, including exercise, heat modalities, and manual therapy (Soares Fonseca, Pereira Silva et al. 2023). Despite the guidelines for treating knee OA prescribe workouts on land or in the water, weight loss, and the use of a cane, alternatives are investigated for pain reduction, including topical NSAIDs, intraarticular corticosteroid injections, and physical modalities like laser therapy. High-intensity laser therapy (HILT), distinguished from low-level laser therapy (LLLT) by its greater output power, has shown positive effects on pain relief, range of motion, and functional improvement in knee OA (Siriratna, Ratanasutiranont et al. 2022). However, the lack of a standardized treatment protocol for HILT and significant variation in study outcomes highlight the need for further research in this area. This study aims to investigate the short-and long-term effects of high-intensity laser therapy combined with rehabilitation exercise on knee pain in adults with early knee osteoarthritis. The study also attempts to evaluate the long-term effects of high-intensity laser therapy combined with rehabilitation exercise on physical function and knee-related disability in adults with early knee osteoarthritis. Additionally, by combining high-intensity laser therapy with rehabilitation exercises, the study aims to investigate the potential disease-modifying effects of the treatment. Specifically, it focuses on how the treatment affects the structural aspects of the knee joint in adults with early-stage osteoarthritis. The study will be carried out using quantitative and qualitative approaches in a parallel-group, randomised, double-blind (subjects and outcomes assessor), placebo-controlled trial design. There will be three stages of it. Phase 1 involves a random allocation of 40 individuals to participate in one of two groups: 20 individuals in group 1 will be treated with high intensity laser treatment with exercise (HILT+E;  $n = 20$ ), while another 20 participants in group 2 will receive exercise and a placebo laser (PL+E;  $n = 20$ ). Each group is scheduled for weekly 60-minute sessions for eight weeks in consecutive weeks. However, phase 2 of the study extends an 12-week follow-up period to investigate the long-term effects of high intensity laser therapy in comparison to placebo laser therapy and exercise. All 40 participants from both groups are

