### **1.4 Research Objectives**

#### **1.4.1 Main Objectives**

- 1) To examine the long-term effects of high-intensity laser therapy (HILT) combined with rehabilitation exercise on knee pain, physical function, and disability levels among adults with early knee osteoarthritis (KOA).
- 2) To investigate the lived experiences and perceptions of individuals with early knee osteoarthritis undergoing the combined intervention of HILT and rehabilitation exercise.

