### **3.1.6 Group allocation and intervention**

In this research, participants will be randomly assigned into one of two groups:

- Group 1 (HILT+E): Participants from this group will undergo individually tailored standard physiotherapy alongside high-intensity laser therapy for twelve weekly sessions. The treatment session will be administered by a qualified physiotherapist who has undergone training in prescribing laser therapy.
- Group 2 (PL+E): Participants will receive individually tailored standard physiotherapy with a placebo/sham intervention once a week for twelve sessions.

Participants in both Group HILT+E and Group PL+E will receive HILT (BTL-6000: 5 W, 1064 nm, 19 to 150 J/cm^2, and 3190 J per session) and sham laser (without emission of energy) as an adjunctive treatment, respectively, in addition to knee rehabilitation exercise (standard physiotherapy care). The specifics of laser interventions based on group allocation are outlined in the attached Appendix, with parameters and procedures derived from manufacturer guidelines (BTL-Corporate, 2020) and previous studies (Kheshie et al., 2014; Ahmad Nazari et al., 2019). To ensure participant blinding regarding their laser intervention, the laser procedures will be identical between groups, including visual light and acoustic indicators (de Paiva et al., 2019). Despite laser therapy being generally safe with few reported adverse effects (Rayegani et al., 2017), this study will implement specific safety measures and precautions. Participants will be required to wear special protective eyewear during laser application, and they will be periodically checked for any discomfort or overheating. Additionally, participants will be asked to report any adverse effects of the laser intervention during the weekly follow-up session.

Qualified physiotherapists from the Hospital Canselor Tuanku Muhriz UKM, unaware of the participants' laser grouping, will administer the personalized physiotherapy treatment,

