### 3.3.3 Ethic consideration and participation confidentially

Research must adhere to ethical guidelines to safeguard the rights and well-being of both researchers and participants. Participants should feel free to voluntarily engage in the study, with the freedom to withdraw at any time if they feel insecure or unsafe during the course of the research. Prior to commencement, participants are provided with and required to read an informed consent form, which outlines potential risks and benefits associated with participation. The research proceeds only upon agreement from the participants.

Data collected is solely utilized for educational purposes, with strict measures in place to ensure the security and confidentiality of participants' identities, facilitated by secure servers. Data will be promptly deleted when it is no longer necessary for the study. Furthermore, researchers refrain from discussing research findings in public forums and remove any identifying information from databases containing sensitive data.

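### Adverse-event screening is specified only at visits during treatment, with none at the three-month follow-up or for participants who stop attending

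*Protocol*

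**What the plan says.** Adverse events are dealt with in two places in the protocol. Section 3.1.7 (Outcome Measures) says that "participants will be screened for potential adverse events, such as bruising, fatigue, weakness, and swelling, during each follow-up visit throughout the treatment". Section 3.1.6 (Group allocation and intervention) says of participants during laser application that "they will be periodically checked for any discomfort or overheating", and adds that "participants will be asked to report any adverse effects of the laser intervention during the weekly follow-up session".

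The long-term visit is described in section 3.1.7: "The assessments are conducted after the intervention occurring three months after the final treatment session at week 24". The outcomes listed there are KOOS, active knee flexion, TUG, NPRS and the knee X-ray, the last at baseline and follow-up only. Neither the entry for that visit nor the outcome list mentions adverse events.

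The first main objective in section 1.4.1 is "To examine the long-term effects of high-intensity laser therapy (HILT) combined with rehabilitation exercise", with pain, function and disability named as the effects. Section 3.3.3 gives participants "freedom to withdraw at any time if they feel insecure or unsafe during the course of the research". No section that I could read says that people who stop are asked why, or are contacted afterwards. Section 3.1.8 keeps everyone in the analysis whatever their adherence.

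The schedule is stated inconsistently. Section 1.1 says "Each group is scheduled for weekly 60-minute sessions for eight weeks in consecutive weeks", followed by 12 weeks of follow-up. Section 3.1.6 gives twelve weekly sessions. Section 3.1.7 puts the post-intervention assessment at week 8 and labels the long-term visit both week 12 and week 24. The budget in section 3.3.4 pays participant travel for 8 sessions and X-rays at weeks 0 and 24.

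**The concern.** When adverse events are collected, and from whom, is a data-collection rule of the protocol. An analysis plan cannot recover events that nobody asked about.

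As worded, both rules end with treatment. The trial would re-measure efficacy and joint structure three months later without asking whether anything untoward had happened in between. A report of sustained benefit beside an adverse-event table that ends at the last session invites the reading that there were no late harms, and the data could not support that.

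Every stated route also needs the participant to be present. Harm that keeps someone away, or that appears after the last attended session, has no stated route into the data.

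**Working it through.** The protocol gives no figure for adverse-event coverage, so there is none to reproduce. The check is a reading of the text followed by a simple division.

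**1. Does the wording reach the three-month visit?** The sentence in section 3.1.7 speaks of follow-up visits, which could at first sight include the long-term one. Two things point the other way. The same sentence limits those visits to the treatment period. Section 3.1.6 also uses the term follow-up for the weekly treatment session. The narrow reading is the natural one. At best the sentence is ambiguous and could be applied either way.

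**2. Does another measurement fill the gap?** Partly.
- KOOS at follow-up has a swelling item, and its pain and daily-living items ask about the last week.
- NPRS records current pain.
- The X-ray shows structural change.
- None of these records the onset, duration, resolution or suspected cause of an event, and none asks about bruising or a skin reaction. A flare that began and settled between the last session and the final week before the visit would not be seen.

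**3. How much time on study has no planned adverse-event question?** The uncovered fraction is (follow-up week − week of last session) / follow-up week, counted from baseline. The post-intervention assessment follows the last session immediately, so it does not change the count.

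| Schedule as stated | Last session | Follow-up visit | Uncovered |
|---|---|---|---|
| 12 sessions; follow-up at week 24 | week 12 | week 24 | (24 − 12)/24 = 12/24 = 50% |
| 8 sessions plus 12 weeks | week 8 | 8 + 12 = week 20 | (20 − 8)/20 = 12/20 = 60% |
| 8 sessions; follow-up at week 24 | week 8 | week 24 | (24 − 8)/24 = 16/24 = 67% |

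Counting three months as 13 weeks after 8 sessions gives 13/21 = 62%, within the same range. The third row takes section 3.1.7 and the budget at face value, but it puts the visit 16 weeks after the last session, which is not three months. The week-12 label cannot be a study week either. With 8 sessions it would fall 12 − 8 = 4 weeks after the last one, and with 12 sessions it would coincide with the last one.

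**4. What happens to people who stop?** They keep whatever was recorded at the sessions they attended, including the in-session checks. What is missing is any stated step to learn why they stopped or what happened next.

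**The case against.** The strongest reply is that this is loose drafting. The screening sentence comes directly after the numbered entry for the long-term visit, and its author may have meant to include that visit. The trial flow chart (section 3.3.5) and the laser appendix cited in section 3.1.6 were not visible in the text I read, so adverse-event wording there cannot be excluded. That lowers confidence that the gap is deliberate. It does not remove the need to correct a sentence that, as it stands, ends screening with treatment.

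A reader might infer more than the document supports:

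- *That follow-up and people who stop yield no safety data at all.* Not so. Attended sessions contribute data, a participant may report the harm at the last one, and the follow-up outcomes capture some worsening.
- *That people who stop because of harm are dropped, biasing the arm comparison towards no difference.* Section 3.1.8 keeps them in the analysis, and nothing bars them from later assessments. The direction of any bias would depend on harm-related stopping by arm, on which the document is silent. The withdrawal sentence in section 3.3.3 is a general statement of voluntariness, not a rule on data collection.
- *That the planned dropout measures the loss.* The 20% allowance is 0.20 × 40 = 8 people, but section 3.1.4 gives no reasons for dropout. The number leaving because of harm could be anything from 0 to 8.
- *That the gap defeats the main objective.* The stated long-term aim concerns pain, function and disability. There is no long-term safety objective.
- *That the small arms make the gap worse.* With no events among 20 people, the one-sided 95% upper bound is 1 − 0.05^(1/20) = 13.9%. That limit comes from the sample size, and better collection would not change it.

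What stands is the narrower point about when, and from whom, adverse events are collected.

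**Conclusion.** The point holds in this form: adverse-event ascertainment is specified only at visits during treatment, and none is specified at the three-month visit or for participants who stop attending. The uncovered span is 50%, 60% or 67% of each participant's time on study, according to the schedule that applies. These figures assume that the screening sentence means what it says and that no unseen page adds to it.

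This is a cheap and worthwhile correction, not a flaw that undermines the efficacy analysis. It matters because the trial sets out to describe long-term effects and will see its participants at three months anyway. The schedule conflict is part of the same point: until the number of sessions and the follow-up week agree, the adverse-event window has no defined end.

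**What to change.** In section 3.1.7, replace the phrase that confines screening to visits during treatment with: *at every treatment session, at the post-intervention assessment and at the three-month follow-up, covering all events since the last contact*. This is the main change.

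As a secondary step, record the reason for stopping, and any related event, for participants who stop, where they agree to be contacted.

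Reconcile sections 1.1, 3.1.6, 3.1.7 and 3.3.4 on the number of sessions and the follow-up week, and state the end of the adverse-event window to match.

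The cost is one extra form at a visit that already takes place and whose X-ray is already budgeted, plus brief contact with those who stop. That contact has no budget line, and because participants may withdraw at any time the consent form must cover it. No extra visit is needed.

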### **3.1.8 Data Analysis**

The data analysis for this study will be conducted using SPSS version 25.0 (SPSS Inc., Chicago, IL, USA) and will adhere to the intention-to-treat principle. All participants, irrespective of their adherence to the intervention, will be included in the analysis. Sociodemographic characteristics of participants at baseline will be described using descriptive statistics and cross-tabulations. The primary statistical analysis for assessing outcomes will involve repeated measures ANOVA, contingent upon meeting assumptions of normality and sphericity. Normality will be evaluated using the Shapiro-Wilk test, with higher values indicating more normal data, while sphericity will be assessed using Mauchly’s test, where lower values closer to 0 suggest more homogenous variance between levels.

The data will undergo two-way repeated measure ANOVA to scrutinize the effects of time, group, and the interaction between the two investigated groups (HILT+E and PL+E). Cohen's d will be applied to ascertain the effect size of each variable, with values of 0.2, 0.5, and 0.8 representing small, medium, and large effects, respectively (Serdar, Cihan et al. 2021). Moreover, the Minimal Clinically Important Difference (MCID) will be considered for the KOOS, NPRS, active knee flexion range, and TUG test to evaluate the clinical relevance of observed changes (Eckhard et al., 2021; Maldaner et al., 2022; Salaffi et al., 2004). All statistical analyses will maintain an alpha level of 0.05 for significance tests (Serdar et al., 2021).

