#### **3.1.4 Sample Size Calculation**

The determination of the sample size for this study will be conducted using G\*Power software version 3.1.9.7, relying on a minimal clinically important difference (MCID) of 11 points for the primary outcome, Knee Injury and Osteoarthritis Outcome Score (KOOS), as indicated by (Eckhard, Munir et al. 2021). We will consider a pre-specified power of 90%, an effect size of 0.3, an alpha level of 5%, and a potential dropout rate of 20%, following the approach outlined by (Serdar, Cihan et al. 2021). Consequently, the necessary total sample size will be 40, with an allocation of 20 participants to each group.

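### The repeated-measures ANOVA fixed in section 3.1.8 drops anyone with a missed visit, so at the planned 20% dropout about 32 of the 40 promised participants are analysed unless values are imputed

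*Protocol*

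**What the plan says.** Section 3.1.8 of the Protocol sets the principle, the population, the method and the software together:

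- Principle: the analysis "will adhere to the intention-to-treat principle".
- Population: "All participants, irrespective of their adherence to the intervention, will be included in the analysis".
- Method: "The primary statistical analysis for assessing outcomes will involve repeated measures ANOVA, contingent upon meeting assumptions of normality and sphericity". The next paragraph adds: "The data will undergo two-way repeated measure ANOVA to scrutinize the effects of time, group, and the interaction between the two investigated groups".
- Software: "The data analysis for this study will be conducted using SPSS version 25.0".

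Section 3.1.4 allows for "a potential dropout rate of 20" per cent in reaching 40 participants, 20 per group. The Executive Summary and section 3.1.7 give three assessments (baseline, post-intervention, follow-up), with X-ray at baseline and follow-up only. Nowhere does the Protocol name imputation, a mixed model or any other way of keeping a participant with a missed assessment in the ANOVA.

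**The concern.** The standard SPSS repeated-measures ANOVA works on one complete row per participant. Someone who lacks one visit is removed from all visits for that outcome, including those they attended. Followed as written, the plan therefore yields a completers analysis for each outcome, while the text describes an analysis of everyone randomised.

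Two things are at stake. Data already collected are thrown away. And if the reasons for leaving differ between the arms, the completers are no longer comparable groups. The second matters most for the follow-up visit, because section 1.4.1 makes the long-term effect the main quantitative objective.

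**Working it through.** **The plan's own sample size.** Inputs from section 3.1.4: "an effect size of 0.3", alpha 5%, "a pre-specified power of 90" per cent, 20% dropout, total 40. The metric of the effect size is not stated; I read it as Cohen's f. For the group-by-time interaction with k = 2 groups and m measurements, λ = f²·N·m/(1−ρ), with degrees of freedom (k−1)(m−1) and (N−k)(m−1). Of the variants tried, only m = 2 and ρ = 0.5 (neither stated in the Protocol) reproduces the figure:

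- λ = 0.09 × 32 × 2 / 0.5 = 11.52 on 1 and 30 degrees of freedom gives power 0.907 at N = 32.
- 32 / 0.8 = 40.

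On that reading the plan needs 32 evaluable people and counts the other 8 as contributing nothing.

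**Participants analysed.** 40 × (1 − 0.20) = 32, about 16 per group if losses are balanced.

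**Collected values discarded, per three-visit outcome** (full data: 40 × 3 = 120; the ANOVA uses 32 × 3 = 96; every baseline assumed observed):

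| When the 8 leave | Values collected | Used by ANOVA | Discarded |
|---|---|---|---|
| After week 8 | 120 − 8 = 112 | 96 | 16 |
| Before week 8 | 120 − 16 = 104 | 96 | 8 (baselines only) |

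In the first case the week-8 standard error rises by √(40/32) = 1.118, about 12%. In the second there are no week-8 values to recover and that loss does not arise. X-ray has two assessments, so there only a missing baseline or follow-up film removes a person.

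**Possible bias.** Nothing in the Protocol fixes these inputs; all are assumptions: SD 15-18 points, equal correlation r between visits, true effect zero, 20% dropout in each arm. In one arm dropout before follow-up depends on the standardised week-8 change through a logistic curve with slope s; in the other it is random. Let k be the mean standardised week-8 change among that arm's completers. Then:

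- Bias in week-8 change = k × SD × √(2(1−r)).
- Bias in follow-up change = half of that, because under equal correlations the two changes correlate 0.5.

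Numerical integration gives k = 0.096 at s = 0.5 and k = 0.227 at s = 1.5. The strong slope means about 49% dropout in the worst quarter of week-8 change and about 3% in the best.

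| Slope s | r | Week-8 bias (SD 15; SD 18) | Follow-up bias |
|---|---|---|---|
| 1.5 | 0.5 | 3.4; 4.1 | 1.7; 2.0 |
| 1.5 | 0.7 | 2.6; 3.2 | 1.3; 1.6 |
| 0.5 | 0.5 | 1.4; 1.7 | 0.7; 0.9 |
| 0.5 | 0.7 | 1.1; 1.3 | 0.6; 0.7 |

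The r = 0.7 rows are the r = 0.5 rows times √0.6 = 0.775. With the same selection in both arms, both shift by k and the difference is zero. Simulations of the same scenarios agree to within about 0.1 point, and a likelihood-type estimate on all available data was within 0.1 point of zero. That last result follows from letting dropout depend only on observed data.

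**Power.** Under the reproducing variant it is 0.907 with 32 and 0.959 with 40. With three assessments and ρ = 0.5 it is 0.961 and 0.988.

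**The case against.** The strongest reply is that the two commitments are not incompatible. Imputing missing visits before the ANOVA would honour both, and an analysis plan not shown here could say so. This stands: a reader might infer that the stated population and method can never be reconciled, and the Protocol does not support that. What remains is that the Protocol names a method that drops these people by default, and gives no sign of imputation.

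It can also be said that the quoted sentence concerns adherence to treatment, not missed assessments, and that the ANOVA is conditional on its assumptions. The first point is right on the wording, although the intention-to-treat commitment beside it is broader. The second helps little, because the stated conditions are normality and sphericity, not completeness.

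On bias, a reader might infer that people who do not improve will leave and that the result will therefore be distorted. The Protocol offers no evidence on who drops out. In a sham-controlled trial with blinded participants, similar selection in both arms is a natural expectation; with no treatment effect it produces no between-group bias. Someone who stops during the course may also leave before week 8, where a mixed model recovers little. These points hold, and they make the bias figures scenarios rather than predictions.

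Finally, a reader might infer that the trial loses its power. On the reading that reproduces the sample size it does not, because the inflation to 40 already allows for 32 evaluable participants.

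**Conclusion.** The point holds as a mismatch between what section 3.1.8 promises and what its named method does by default. At the planning rate about 8 of 40 participants leave each three-visit analysis unless their values are imputed; the number changes with the actual dropout and with any further missed visits.

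The certain cost is discarded data: up to 16 values per three-visit outcome, with a week-8 standard error about 12% larger if the losses come after week 8. The bias is conditional on selection that differs between arms. At follow-up, the visit that matters most for the main objective, it is 0.6 to 2.0 points across the scenarios shown, under a fifth of the 11-point MCID (2.0/11 = 0.19). At week 8 it reaches 4.1 points, a little over a third (4.1/11 = 0.37). Both are biases in change from baseline and rest on the assumed SD, correlation and dropout slope.

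This should be fixed, but the sizes do not make it critical.

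**What to change.** In section 3.1.8, replace the repeated-measures ANOVA with a linear mixed model for repeated measures (SPSS MIXED, REML) with group, visit and group-by-visit as fixed effects and an unstructured covariance across visits. Fit it to all available visits of everyone randomised, analysed as randomised. Say explicitly that participants with missed assessments stay in the analysis. The sphericity condition then falls away.

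Add one sensitivity analysis for data missing not at random, for example imputing dropouts' missing values with a shift whose range is fixed before unblinding. It is needed because the mixed model is valid only if missingness depends on observed data, and because it recovers little for people who leave before week 8. Multiple imputation ahead of the ANOVA would also honour the stated population, but would have to be written into the section.

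The cost is a change of wording and slightly more analysis work. Software, visits, data and sample size stay as they are.
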